#### 3. Nutritional supplements (seal oil and soy oil)

Findings from patients with inflammatory bowel disease (IBD) suggest that seal oil may reduce musculoskeletal pain. IBD patients report high levels of comorbidity, including musculoskeletal pain [66]. A substantial amelioration of joint pain after short-term administration of seal oil, has been reported in one pilot study [35], and one controlled study [36]. In Bjørkkjær et al. [67] prostaglandin E_2 _(PGE_2_) levels were also reduced. Given these findings, testing a possible effect of seal oil in LBP patients seems a reasonable next step, and an ethically acceptable experiment. In addition, with the current interest in alternative medicine in the Norwegian population, seal oil seems to have high face validity as a potential effective supplement for muscle pain.

Patients randomized to nutritional supplements, will receive commercially available seal oil for the same duration as the CBT treatment, in a double-blind randomized, controlled design. Oils will be administered as 20 capsules daily, providing 638 mg EPA, 399 mg DPA, and 798 mg DHA per day for those receiving seal oil, and 5.31 g linoleic acid (18:2n-6) per day for those receiving soy oil. Before meals, 10 capsules should be taken in the morning and 10 capsules in the evening, with fluid. Capsules will be stored at room temperature in blinded light-protected boxes during the study. Capsules are chosen because they are easy to administrate, have no taste, less regurgitation problems, and are easier to blind, compared to using the oils in liquid form. Testing of the oils before the intervention showed that vitamin A, i.e. sum retinol (13-, 11-, 9-cis) and all trans retinol, i.e. A_1 _and 3,4 didehydro-all-trans retinol (A_2_) in both oils were below 0.28 mg/kg. Vitamin D_3 _content in daily soy oil and seal oil dosages were 1 μg and 0 μg respectively. The antioxidant D-alpha-tocopherol was added in the case of seal oil, giving a vitamin E (alpha-tocopherol) content in seal oil and soy oil of 85.4 and 16.6 g/100 g respectively. The seal oil contains 56.6 g/100 g monounsaturated fatty acids, which are less prone to lipid peroxidation than polyunsaturated fatty acids (PUFAs), and the oil has no known major adverse effects [35,36]. Soy oil is common in the diet in the western world, and is considered a placebo in this trial. Cholesterol levels in seal oil and soy oil were 36.8 and 2.9 g/100 g respectively. The seal oil is a refined oil from the blubber of adult harp seals (*Phagophilus groenlandicus*). The soy oil is a refined oil from soybeans, which are GMO-free. Both oils were approved according to current legislations on contaminants and relevant quality standards

### Drop out from randomized treatment

Participants who drop out of treatment will be asked if they are willing to continue filling out questionnaires. Those who wish to continue contributing data to the study, but who are not able to or decline to come to the clinic, will receive the questionnaires by mail, together with pre-paid return envelopes.

### Assessment and Procedures

All participants will fill out questionnaires at the clinic immediately before BI. Follow up is conducted at 3, 6, and 12 months after the first session of BI. Data on sick leave will be obtained from the Norwegian National Insurance Administration (see outcome), and will also be collected 24 months after randomization (Figure 1).

### Measures

#### Primary outcome measures

The main outcome in the study is sick leave. The data on sick leave/insurance status will be based on register data from the Norwegian National Insurance Administration.

#### Secondary outcome measures

##### Questionnaires

Standard forms contain items for demographics, medication, previous treatments, pain intensity, and life style variables. Below follows a short description of the most important questionnaires, all validated and in Norwegian:

1. Subjective Health Complaints (SHC): The SHC-inventory records complaints without asking for attributions or medical diagnosis [68]. The selection of items is not based on any specific theory, but covers the most frequent health complaints and reasons for being seen by a general practitioner [69]. The inventory has 5 subscales; musculoskeletal, pseudoneurological, gastrointestinal, flu, and allergy complaints, and covers the period of the previous 30 days. The reliability and validity are good [68].

2. Illness Perception Questionnaire Revised (IPQ-R): This scale has five subscales providing information on the five components underlying the cognitive representation of the illness. These are: identity (the symptoms that the patient associates with the illness), cause (personal ideas about etiology), timeline (the perceived duration of the illness), consequences (expected effects and outcome) and cure-control (how one controls or recovers from the illness). The internal consistency, validity, and test-retest reliability of the separate scales have been found to be good [70].

3. Oswestry Disability Index [71] and Norwegian Function Assessment Scale [72] both assesses functional limitation. Reliability and validity of the Oswestry Disability Index have been found to be good [73]. The Norwegian Function Assessment Scale has 7 sub domains, and reliability and validity have been tested and found good [74].

4. Hospital Anxiety and Depression Scale (HAD) and Hopkins Symptom Checklist (HSCL) both assesses mood. The HAD scale has been found to be a reliable instrument for detecting states of depression and anxiety, and the anxiety and depressive subscales are also valid measures of severity of the emotional disorder [75]. The scale avoids overlap with somatic symptoms of physical illness. The HSCL-25 scale consists of 25 questions about the presence and intensity of the most common symptoms of anxiety and depression [76].

5. [name] Fatigue Scale: This is an 11-item scale measuring physical and mental fatigue. The sum score can range from 0 to 33; a bimodal score ranging from 0-11 can also be obtained. The fatigue scale has been used extensively in research and has good psychometric proprieties [77]. It has also been validated in Norwegian [78].

6. Fear Avoidance Beliefs Questionnaire (FABQ): This is a scale that measures self-reported fear avoidance thoughts and beliefs in LBP patients [79]. It has 2 subscales; fear avoidance for physical activity and fear avoidance for work. Reliability and validity was tested in a Norwegian population of LBP patients and found to be acceptable [80].

7. Pain Stages of Change Questionnaire (PSOCQ): This is a scale measuring motivation to change. It is a multidimensional instrument designed to measure readiness to change in individuals with chronic pain [81]. Five stable subgroups have been identified and named: Pre-contemplation, contemplation, non-contemplative action, participation, and the ambivalent subgroup [82].

8. A mini-version self-administrated food frequency questionnaire (FFQ) has been developed, with focus on habitual intake (i.e. last year) of fish and other seafood for dinner, as sandwich spread, in salads or as snack. The questions relate to type of seafood, frequency of intake and in some cases portion size. It also includes questions about the use of long chain omega-3 PUFA supplements (fish oil, seal oil etc.).

##### Psychiatric Interview

The Mini-International Neuropsychiatric Interview (MINI) was applied as the structured diagnostic interview [58] for DSM-IV [83] and ICD-10 [84] assessing psychiatric disorders. It is a short structured diagnostic interview, developed jointly by psychiatrists and clinicians in the United States and Europe. It is based on "yes" and "no" answers and covers 23 Axis 1 disorders. In the multiaxial system of DSM-IV, Axis I disorders include all major mental disorders as well as developmental and learning disorders. The MINI interview usually takes 15-20 minutes, and has high reliability and validity [58]. We used the Norwegian version of MINI Plus [85].

### Blood samples

For a selected number of participants, fasting venous blood samples are drawn and stored in -80°C freezer for later analysis, or in a -20°C freezer for 4 weeks, before subsequent rapid analysis. The samples will be taken before and after the interventions, using validated methods at the NIFES [86] with modifications. Fatty acid composition will be measured in unwashed erythrocytes, to get information on compliance, and possible corroboration to any treatment effect. Extra vials of unwashed erythrocytes and plasma at inclusion and after 3 months will be stored in a bio bank for a possible future balanced risk assessment (nutrients and contaminants in same sample) of seafood intake.

### Saliva samples

Previous studies have shown that cortisol measured through saliva using salivette, is a reliable and valid measure of unbound and free cortisol level in plasma [87]. Saliva cortisol will be measured in order to assess the cortisol day curve (stress profile). Furthermore, the aim is to investigate if the different treatments affect the cortisol profile. The participants collect saliva on two consecutive days between Tuesday and Friday at baseline and 3 months later. Four saliva samples will be collected each day; immediately after awakening, 30 minutes later, and at 3 pm and 10 pm. Participants will be asked to avoid food, drinks and nicotine 30 minutes before collecting saliva, and keep a written record of the exact time of awakening and saliva collecting. The participants keep the saliva samples in their freezer at home, before bringing them to the laboratory for analyses.

### Analyses

#### Sample size calculations

The sample size calculations were based on data from Hagen et al. [30] and the transition probabilities calculated for the intervention group in that study. The sample size was based on the transition probabilities at 9 months, where approximately 40% of the individuals had returned to work. Hagen et al. [59] found that the effects were largest for the earlier period after the intervention. This is therefore an argument to use 40% off sick leave at 9 months as the most relevant measure for effect in this study. This was compared to a hypothesized 60% return to work (RR 1.5) as an adequate effect size. The sample size calculations were based on standard formulas for calculating sample size, for studies comparing binomial proportions using the statistical package "R" (Library Hmisc). This may increase the power of the estimates in the analyses, since the simpler method used for the calculation does not include in this issue. All calculations were based on a power of 80% and a significance level of 5%.

Separate sample size calculations for males and females were computed. The total number of individuals should be approximately N = 4*n, where n is the calculated sample size and 4 is the number of arms in the study. The total number of males should be N = 4*65 = 260 and the total number of females N = 4*81 = 324. If we control for gender in the analysis instead of performing stratified analyses, we do not need to calculate separate sample sizes for men and women. The total number of participants should be 97 in each arm (N = 388). These numbers require a multi-centre design.

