### Evidence based treatments for LBP

The treatment principles applied in this study follow the evidence-based guidelines for the treatment of CLBP, developed in Europe (http://www.backpaineurope.org)[27]. The recommended treatments include conservative treatments like CBT, supervised exercise therapy, brief educational interventions (BI), and multidisciplinary bio-psychosocial treatments. A recent review of psychological treatments for CLBP, provide support for the efficacy of psychological interventions, including CBT, among persons with CLBP [28]. While the evidence points to BI and CBT as effective treatments, many of the studies included in the review, are at risk of bias because of methodological problems, and it has been argued that confidence in the results are unwarranted [29]. BI's are associated with positive outcomes for return to work early in the process [30]. However, it is still unclear whether the effect would be as beneficial later on, when the patients may develop behavior that adversely affects their illness and recovery. Some studies have shown that CBT is effective in reducing pain, while other studies have shown beneficial effects on physical and mental function and sick leave rates, but not pain [31,32]. It is difficult to replicate studies and results of the effects of CBT, because the components of the therapy and the experience of the therapists vary, and the treatment protocols are rarely documented. The European Guidelines for treatment of chronic low back pain emphasize the need to evaluate the effectiveness of using CBT-therapists without formal training in clinical psychology. These issues will be addressed and answered in the current trial; the CBT treatment protocol will be documented in a manual, and the treatment will be monitored closely. Therapists with different professional backgrounds will be recruited, trained, and followed in order to apply the protocol.

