A treatment manual has been written by [name] & [name] [63], and developed in close collaboration with experienced specialists in family medicine, psychiatry, and physical medicine and rehabilitation, all educated in cognitive behavioral therapy ([name], [name], [name] and [name]). LBP patients seem to be sensitive to conflicting messages. Even small changes in the information given, may bring back the fear and avoidance behavior [64]. This requires both a detailed manual, and consistent training and supervision of the clinicians. The CBT-clinicians in this study are all health care personnel with varied backgrounds; six MD's with a specialty in physical medicine and rehabilitation, two psychologists, one psychiatric nurse, and one physiotherapist. All had to undergo a general CBT-course (with a minimum duration of 10 days and 15 hours of group supervision), or be familiar with CBT from previous education and training. In addition, all CBT-clinicians received three days of training in this LBP-tailored CBT, followed by at least one individual session with a patient not included in the study. The session is recorded on videotape, and rated by the supervisors and the first author of the treatment manual ([name]). The session will be rated according to protocol adherence, and satisfying quality of the CBT. All clinicians have to be approved before treating patients included in the trial. All CBT sessions in the trial will be audio taped. Tapes will be used for supervision as well as rating for research purposes. Supervision is offered approximately every 4^th ^month, but the clinicians are offered phone and email contact with supervisors when needed. A random selection of the tapes are continuously evaluated by independent raters ([name] and graduate students in psychology), with a percentage evaluated twice for inter rater reliability, using a modified Norwegian version of the Cognitive Therapy Adherence and Competence Scale [65].

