### Analysis strategy

#### Primary analyses of efficacy

Sick leave/insurance status will be calculated as risks of shifting between different states of sick leave, disability pension, and recovered. The outcome from the participating clinics will be combined if no gross center effect is found. The analyses will follow the "intention to treat" principle. Per protocol analysis will also be performed. The proportions of participants with a positive primary outcome will also be compared across the treatment groups. If there are significant differences, we will estimate the number of participants that need to be treated in order for one additional participant to benefit (NNT), compared to the least effective therapy. A Cox-proportional hazards model may model the transitions between the different states. Regression models for the transition probabilities will also be performed. Explanatory variables (treatment) and confounders (e.g. age, gender) will be included as in any regression model. Possible changes in diagnosis and other characteristics will be built in. Partial recovery represented by partial sick leave will be accounted for.

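### The 97 per arm and 80% power assume independent patients, but CBT is given by ten clinicians; for CBT comparisons, power should be stated as a range over an assumed therapist ICC, with therapist allowed for in that arm

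*Protocol article*

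**What the plan says.** Under Sample size calculations, the control rate comes from an earlier trial: "The sample size was based on the transition probabilities at 9 months, where approximately 40% of the individuals had returned to work". The target is set next: "This was compared to a hypothesized 60% return to work (RR 1.5) as an adequate effect size". A standard formula for two binomial proportions, at 80% power and 5% significance, leads to "The total number of participants should be 97 in each arm (N = 388"). No ICC, design effect or other clustering allowance appears. Number and source of participants gives a recruitment goal of 400, or 100 per arm if allocation is equal.

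Under Treatment interventions, section 2 (BI and CBT), CBT is seven individual sessions over two to three months. The clinicians are "six MD's with a specialty in physical medicine and rehabilitation, two psychologists, one psychiatric nurse, and one physiotherapist", which is ten people. The same section describes a treatment manual, training, approval before treating trial patients, taping of sessions and supervision. Therapists' compliance with treatment manuals adds adherence checks on a sample of sessions.

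Primary analyses of efficacy pools the clinics unless a gross centre effect is found. On the models it says: "Explanatory variables (treatment) and confounders (e.g. age, gender) will be included as in any regression model". Therapist is not mentioned.

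**The concern.** Patients who share a therapist tend to have more similar outcomes than patients who do not. In this design the extra layer exists in one arm only: every patient receives BI, and the oil arms add no therapist. Therapist variation in the CBT arm therefore does not cancel in a comparison of CBT with another arm.

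The comparisons affected matter. Superiority of CBT on return to work and sick leave is the first efficacy hypothesis, sick leave is the primary outcome, and both primary objectives involve the CBT arm. With any positive therapist ICC, one of two things follows. An analysis that allows for therapist has less power than the stated 80%, or one that ignores therapist has standard errors that are too small and a type I error above 5%. These are alternatives and do not add up. Comparisons without the CBT arm are unaffected.

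**Working it through.** **Inputs from the Protocol article.** Rates 0.40 and 0.60, power 80%, significance 5%, 97 per arm (Sample size calculations); ten CBT clinicians (section 2, BI and CBT); recruitment goal 400 (Number and source of participants).

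**Inputs assumed.** A two-sided test (sidedness is not stated, but two-sided reproduces the figure); one treating therapist per CBT patient; equal caseloads; ICC of 0.01 to 0.10.

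**Step 1: reproduce the plan's figure.** Two-sided, pooled variance under the null, no continuity correction, mean rate 0.50:

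n = [1.96·√(2·0.25) + 0.8416·√(0.24 + 0.24)]² / 0.20² = (1.3859 + 0.5831)² / 0.04 = 96.9, so 97 per arm.

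Power at 97 per arm is 80.0%, an exact match. The alternatives do not match: 107 with continuity correction, 77 one-sided, 95 with unpooled variance. The 97 is correct arithmetic under independence.

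**Step 2: put clustering in the CBT arm only.** Mean caseload m = 97/10 = 9.7, and design effect DE = 1 + (m − 1)·ICC. Then:

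- SE under the null: SE₀ = √[0.25·(1 + DE)/n]
- SE under the alternative: SE₁ = √[0.24·(1 + DE)/n]
- Power = Φ[(0.20 − 1.96·SE₀)/SE₁]

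Example at ICC 0.05: DE = 1 + 8.7·0.05 = 1.435; SE₀ = 0.0792; SE₁ = 0.0776; power = Φ[(0.20 − 0.1553)/0.0776] = Φ(0.576) = 71.8%.

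**Step 3: type I error if therapist is ignored.** The unadjusted SE is √[2/(1 + DE)] times the correct one, so the two-sided error is 2·{1 − Φ(1.96·√[2/(1 + DE)])}. At ICC 0.05 the ratio is 0.906 and the error 7.6%.

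| ICC (assumed) | DE | Effective CBT n | Power, 97 per arm | Power, 100 per arm | Unadjusted SE / correct SE | Type I error, therapist ignored |
|---|---|---|---|---|---|---|
| 0 | 1.00 | 97 | 80.0% | 81.2% | 1.00 | 5.0% |
| 0.01 | 1.09 | 89 | 78.3% | 79.5% | 0.98 | 5.5% |
| 0.02 | 1.17 | 83 | 76.6% | 77.8% | 0.96 | 6.0% |
| 0.05 | 1.44 | 68 | 71.8% | 72.8% | 0.91 | 7.6% |
| 0.10 | 1.87 | 52 | 64.5% | 65.4% | 0.84 | 10.2% |

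The 100-per-arm column uses m = 10. The other columns are for 97 per arm.

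**Step 4: sensitivity.** Uneven caseloads lower power further. With an assumed coefficient of variation of 0.6, DE = 1 + [(1 + 0.6²)·m − 1]·ICC, and power at 97 per arm is 77.6%, 75.3%, 68.7% and 59.5% for the four positive ICCs. Having only ten therapists also costs degrees of freedom: a Satterthwaite t test (9 df for the CBT arm, unpooled variance, equal caseloads) gives 76.9%, 75.0%, 69.7% and 61.9%.

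**The case against.** The strongest reply is that this is largely an omission in a condensed article. A therapist effect is detail that an analysis plan commonly supplies, and the covariate list is introduced by way of example, so it is open. A reader might infer that the primary models exclude therapist and that standard errors will be too small. The documents do not support that: the type I error column is a risk conditional on the final analysis. The sizing is different, because it is completed in this article and can be judged as it stands.

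A reader might also take the remark that CBT studies are hard to replicate "because the components of the therapy and the experience of the therapists vary" as an admission about this trial. In context, under Evidence based treatments for LBP, it describes earlier studies, and the trial's manual and monitoring are offered as the answer. Those measures may well keep the ICC low. They are not a statistical allowance, and they do not make it zero.

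Third, the size rests on an ICC that the documents do not give. It is tempting to say that power is clearly below 80%. At ICC 0.01 the loss at 97 per arm is under 2 points, and the goal of 400 brings power to 79.5%. Nothing in the documents establishes a value of 0.05 or more for register-based sick leave.

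Finally, randomisation is stratified by clinic, and clinic effects shared by all arms largely cancel, so only therapist variation beyond clinic counts. The article also suggests, in an unclear sentence, that the planned analysis may have more power than the simple binomial method. Both points narrow the claim, but neither supplies a therapist allowance.

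**Conclusion.** The point holds in a limited form. The 97 per arm is not an arithmetic error, but it yields 80% power for CBT comparisons only if the therapist ICC is zero. With ten even caseloads, power at 97 per arm runs from 78.3% at ICC 0.01 to 64.5% at ICC 0.10, and from 79.5% to 65.4% at the recruitment goal. Excess type I error, from about 5.5% to 10.2%, arises only if the final analysis leaves therapist out.

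The direction is certain for any positive ICC; the size is not. It is minor near 0.01 and material from about 0.05, where roughly 8 points of power are lost (80.0% − 71.8% = 8.2). The figures rest on the assumed ICC, one therapist per patient, equal caseloads and a normal approximation. Uneven caseloads and a small-sample correction would both lower power further.

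**What to change.** 1. Record the treating therapist for every CBT patient.
2. In each primary comparison that involves the CBT arm, allow for therapist in that arm only. Use a partially nested random effect (a frailty term in the Cox model), or a therapist-clustered variance with a small-sample correction, with patients in the other arms treated as singletons.
3. In Sample size calculations, replace the flat 80% for CBT comparisons with a range and state the ICC assumed, for example about 72% at ICC 0.05 with 97 per arm.

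If the full analysis plan already contains a therapist term, only items 1 and 3 need checking. The cost is one recorded variable and one model term, slightly wider intervals for CBT comparisons, and a less favourable stated power. No extra patients are needed. For information, restoring 80% power with ten equal caseloads would take 102, 107, 125 or 179 per arm at ICC 0.01, 0.02, 0.05 or 0.10.
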